**4.h The PIC Partners study and HIV-1 drug resistance in transmission pairs**

In 1997, Liu et al. [159] reported a partner-pair enrolled in the PIC Cohort study who concurrently acquired HIV-1 infection from a common source partner and subsequently experienced widely divergent courses of HIV-1 disease progression. Following identification of these subjects, SeaPIP investigators developed a greater interest in studying HIV-1 transmission pairs to understand host-virus interactions and the relationships between viral diversity, viral pathogenesis, and immune system control. An early analysis of the study described the results of partner referral for 38 subjects enrolled in the PIC cohort [186]. Eighteen (47%) of these subjects had potential source partners who were identifiable. In two instances, both members of the partner-pair developed primary HIV-1 infection and were counted in this total of 18 until the direction of transmission could be determined. Four partners were not evaluated. One partner was repeatedly HIV-negative. In ten (91%) of the remaining 11 partnerships, the transmission relationship was confirmed; these confirmed transmission pairs represent 26% of PIC enrollees during this study period.

The PIC Partners Study remains an active collaboration funded by SeaPIP (NIH P01 AI-57005: Immunology and Virology of Acute HIV Infection) and a Mentored Career Development Award to [name] (NIH K23 AI-65243: Primary HIV-1 Infection: The Public Health Perspective) [159, 173, 186, 187]. To date, *36* potential source partners have been enrolled in either the PIC Cohort or PIC Partners studies; *32* of these partners were enrolled after 1996. *Nineteen* potential source partners have been confirmed as the source of HIV-1 infection in the PIC enrollee. **Table 6** shows demographic and other characteristics of confirmed source partners. Confirmatory studies on the remaining partner-pairs are pending.

**5. Research Design and Methods**

**5.a Overview of study design and rationale**

The studies proposed in this section will provide a better understanding of the prevalence and dynamics of low-frequency HIV-1 drug resistance mutations in ARV-naïve subjects during primary HIV-1 infection (**Aim #1**), the impact of low-frequency drug resistance mutations on response to ARV therapy (**Aim #2**), and the relative "transmission fitness" of mutant viruses (**Aim #3**). The project will be powered to perform the longitudinal analyses described in the first two studies with use of samples from *approximately 100* subjects who previously enrolled in the PIC Cohort study within 30 days after HIV-1 infection and from *80* subjects who will be enrolled prospectively. Eligibility will be restricted to subjects who acquired HIV-1 infection after 1996, when highly active ARV therapy became widely available in Seattle. OLA will be used to evaluate HIV-1 drug resistance in the PBMCs, blood and seminal plasma from ARV-naïve PIC subjects at baseline (the first available specimen), and 6 and 12 months after HIV infection (**Aim #1)** and in PBMCs 6 and 12 months after the start of ARV therapy (**Aim #2)** to detect changes in the levels of low-frequency HIV-1 drug resistance over time.

The third aim will study PIC subjects and their source partners enrolled in the PIC Cohort and PIC Partners studies. After the transmission relationships are confirmed by molecular methods, this cross-sectional analysis will compare the results of HIV-1 drug resistance testing performed on PBMCs and blood plasma from PIC subjects with the results of resistance testing performed on PBMCs, blood plasma, and genital secretions from their confirmed source partners. The partner-pairs studied in this third aim will also include retrospective analysis of previously collected specimens and continued prospective enrollment in order to maximize the precision of estimates of "transmission fitness" to be described in **5.c.3 Aim #3**.

The studies proposed in this application require access to a cohort of subjects with acute HIV-1 infection to identify transmitted low-frequency HIV-1 drug resistance that may quickly fall below the limits of detection after HIV-1 acquisition and to study transmission pairs as proximal as possible to the transmission event. The Seattle Primary Infection Program and the UW Primary Infection Clinic are ideally suited to perform these studies. Established in 1992, the PIC has enrolled and followed over 300 subjects with acute and early HIV-1 infection, and our ongoing PIC Partners study was specifically designed to provide insights into the biologic and behavioral correlates of HIV-1 transmission. Given the high prevalence of transmitted low-frequency mutations identified by our pilot project, these two established cohorts are logical populations in which to study the transmission of HIV-1 drug resistance and dynamics following HIV-1 acquisition. The OLA, developed by collaborator [name], is a relatively inexpensive, high-throughput assay that can screen for HIV-1 drug resistance at 17 codons associated with primary drug resistance. It is an obvious choice, from among the more-sensitive HIV-1 drug resistance assays, for these studies.

**Aim #2:**

Detection of new mutations during ARV therapy

Source partners

OLA in:

PBMCs

Blood plasma

Genital secretions

Baseline HIV-1 drug resistance mutations detected

**Aim #3**:

Transmission of HIV-1 drug resistance

PIC enrollees

Baseline consensus sequencing and OLA in:

PBMCs

Blood plasma

Semen

OLA in PBMCs, blood and/or seminal plasma 6 and 12 months after HIV-1 infection

**Figure 5: Overview of the proposed research project and specific aims**

Baseline HIV-1 drug resistance mutations not detected

ARV therapy

OLA in PBMCs 6 and 12 months after ARV start

**Aim #1:**

Detection of mutations in untreated subjects over time

**Figure 5:** Baseline HIV-1 drug resistance testing will be performed using OLA and consensus sequencing on the first available specimens from subjects with acute and very early HIV-1 infection who enroll in the PIC cohort and from subjects previously enrolled in the cohort who meet eligibility criteria for study. ARV-naïve subjects with mutations detected at baseline will provide specimens to determine the detection of mutations over time (**Aim #1**). Subjects both with and without HIV-1 drug resistance at baseline who initiate ARV therapy during follow-up will provide specimens to determine whether increased levels of HIV-1 drug resistance mutations are detected in PBMCs during ARV therapy and whether low-frequency mutations impact the response to ARV therapy (**Aim #2**). Subjects enrolled in the PIC Cohort study will refer potential source partners to the PIC Partners study. Partners will be asked to provide blood and genital specimens in order to compare patterns of HIV-1 drug resistance within transmission pairs (**Aim #3**).

**5.b Study objectives**

**Aim #1: Determine whether the "level" of detection of HIV-1 drug resistance variants predicts the duration of detection of these variants over time since HIV-1 acquisition.**

Primary objectives:

1) Quantify the proportion of subjects with transmitted HIV-1 drug resistance that have mutations that remain detectable in PBMCs compared to blood plasma 6 and 12 months after HIV-1 infection.

2) Compare the proportion of subjects with low-frequency HIV-1 drug resistance that have mutations that remain detectable 6 and 12 months after HIV-1 infection compared to subjects with mutations detected by consensus sequencing at baseline.

Secondary objectives:

1) Identify subject characteristics associated with transmitted low-frequency HIV-1 drug resistance.

2) Compare the detection of mutations in blood and seminal plasma in male subjects over time.

3) Describe differences in the detection of specific drug resistance mutations (e.g. M184V) over time.

**Aim #2: Quantify the increase in detection of low-frequency mutations in PBMCs during ARV therapy.**

Primary objectives:

1) Compare the proportion of subjects with transmitted HIV-1 drug resistance that have new HIV-1 drug resistance mutations detected in PBMCs 6 and 12 months after the start of ARV therapy compared to subjects without transmitted HIV-1 drug resistance at baseline.

2) Evaluate time to virologic suppression in subjects with transmitted HIV-1 drug resistance compared to subjects without transmitted HIV-1 drug resistance.

Secondary objectives:

1) Explore whether the timing of ARV therapy impacts the increased detection of low-frequency mutations, time to virologic suppression, or time to virologic failure.

2) Explore whether specific mutations (e.g. M184V) are selected for by ARV therapy and are found at a greater level over time within treated subjects with and without HIV-1 drug resistance at baseline.

3) Explore whether specific HIV-1 drug resistance mutations are associated with significant differences in time to virologic suppression and time to virologic failure compared to subjects without transmitted HIV-1 drug resistance.

**Aim #3: Compare HIV-1 drug resistance patterns in PIC subjects and their source partners.**

Primary objective:

1) Quantify the probability of transmission of HIV-1 drug resistance mutations from source partners.

Secondary objectives:

1) Explore whether the probability of transmission differs for specific drug resistance mutations.

2) Explore whether HIV-1 drug resistance mutations are found at different levels in recipient partners compared to confirmed source partners.

**5.c Study design and data analysis**

**5.c.1 Aim #1: Determine whether the "level" of detection of HIV-1 drug resistance variants predicts the duration of detection of these variants over time since HIV-1 acquisition.**

Aim #1 will evaluate *the level* of detection of low-frequency HIV-1 drug resistance mutations in PBMCs, blood and seminal plasma from ARV-naïve subjects at baseline and over time. Because we anticipate that no more than 50% of male subjects will provide semen specimens and we will have few female subjects available for study, the study will be powered to compare transmitted HIV-1 drug resistance in PBMCs and blood plasma. We hypothesize that a smaller proportion of subjects will have low-frequency mutations that remain detectable compared to subjects with mutations detected by consensus sequencing at baseline, and a greater proportion of subjects will have mutations that remain detectable in PBMCs compared to blood and seminal plasma.

All subjects selected for study will have baseline testing to detect transmitted HIV-1 drug resistance using both OLA and consensus sequencing. Results of baseline testing will be combined with results from our pilot study to obtain a more precise estimate of the prevalence of transmitted HIV-1 drug resistance in Seattle. Logistic regression analyses will explore subject characteristics potentially associated with transmitted drug resistance including subject age; race/ethnicity; level of education; risk factor for HIV-1 acquisition; year of HIV-1 acquisition; use of methamphetamine, other illicit drugs, or erectile dysfunction medications; number of recent sex partners; and locations for meeting new partners (e.g. bathhouses, internet, etc) [188, 189].

**Table 7: Precision estimates for proportions of subjects with transmitted HIV-1 drug resistance**

| Sample size | 100 | 150 | 200 | 300 | 400 |
| --- | --- | --- | --- | --- | --- |
| 95% confidence interval (+/-) | .10 | .08 | .07 | .06 | .05 |

The sample size required for this study will be motivated by a longitudinal analysis that will compare the proportion of subjects with transmitted HIV-1 drug resistance who have mutations that remain detectable in PBMCs and blood plasma 6 and 12 months after HIV-1 infection. In contrast to a strategy that tests every specimen until mutations can no be longer detected, this testing framework will minimize the numbers of tests to be performed as part of this study and will inform the design of future testing strategies to determine more precisely the time to loss of detection of transmitted low-frequency HIV-1 drug resistance mutations.

**Table 8: Estimated number of subjects with mutations in PBMCs and plasma over time**

| **8a**: Distribution of subjects at baseline | | | |
| --- | --- | --- | --- |
|  | | plasma | |
| - | + |
| PBMCs | - |  | *14 (41%)* |
| + | *8 (24%)* | *12 (35%)* |

| **8b**: Distribution of subjects at follow-up | | | |
| --- | --- | --- | --- |
|  | | plasma | |
| - | + |
| PBMCs | - | 12 (30%) | 4 (10%) |
| + | 18 (45%) | 6 (15%) |

| **8b**: Distribution of subjects at follow-up | | | |
| --- | --- | --- | --- |
|  | | plasma | |
| - | + |
| PBMCs | - | *20 (25%)* | *16 (20%)* |
| + | *40 (50%)* | *4 (5%)* |

+ = subjects w/ ≥1 mutation or mixture.

- = subjects w/o mutations or w/ indeterminate results

**Table 8**: The number of subjects who would have transmitted drug resistance identified in PBMCs and plasma at follow-up (**Table 8b and 8c**) was estimated for power calculations *based on the distribution of mutations identified at baseline (****Table 8a****) from the pilot project.*

Power calculations were performed using a two-sided McNemar's exact test with significance level of 0.05. We assumed that the baseline distribution of subjects with mutations in PBMCs, plasma, or both would be similar to that found in the pilot study *(****Table 8a):*** *25% in PBMCs, 40% in plasma, and 35% having mutations in both PBMCs and plasma).* In these power calculations, we estimated the proportion of these subjects who would have mutations detected in PBMCs and/or plasma *at the* follow-up *evaluation* (**Table 8b and *8c***). If *mutations initially detected in PBMCs and plasma remain detectable in 100% and 25% of subjects, respectively, in the follow-up specimen,* 30% of subjects who had transmitted HIV-1 drug resistance *will* no longer have detectable mutations, 10% of subjects *will* have mutations detected in plasma only, 45% of subjects *will* have mutations detected in PBMCs only, and 15% of subjects *will* continue to have mutations detected in both PBMCs and plasma (***Table 8b***). *With this distribution,* we would have 84% power to determine whether a significant difference exists in the detection of mutations in PBMCs versus plasma over time with 40 subjects who had transmitted HIV-1 drug resistance detected at baseline.

*If the difference in loss of detection between PBMCs and plasma is less extreme, and 67% and 13% of mutations initially detected in PBMCs and plasma remain detectable in follow-up (****Table 8c****), then we would have 89% power to determine whether a significant difference exists in the detection of mutations in PBMCs versus plasma over time with 80 subjects who had transmitted HIV-1 drug resistance detected at baseline. Note that the McNemar's exact test takes account only of the distribution at follow-up and not changes over time; these calculations are therefore extremely conservative compared to the planned analysis described below.*

This sample size will be generated from previously enrolled subjects and from new enrollment. *There are 73 subjects among the entire PIC cohort who enrolled within 30 days of HIV-1 infection, who enrolled after 1996, and who have a median of 36 (range 0-139) months in follow-up.* Nine subjects studied through the pilot project were enrolled within 30 days of HIV-1 infection, had at least one low-frequency mutation identified, and have at least one year of follow-up in the cohort without ARV treatment. *Fifty-four subjects have enrolled in the cohort since the end of the pilot project, and we* anticipate that there will be an additional *15* subjects who will enroll before the start of this project, all of whom *will have been* enrolled within 30 days of HIV-1 infection. If we assume that *34*% of these subjects would have HIV-1 drug resistance mutations and *66% will remain ARV-naïve and in follow-up for at least one year*, we would expect that *15 previous-enrolled subjects will be eligible for study in Aim #1*. Prospective enrollment of *16* subjects with transmitted HIV-1 drug resistance in addition to the *24* previously-enrolled subjects would achieve the desired total sample size of 40. If *34*% of newly-enrolled subjects have transmitted HIV-1 drug resistance but *33*% of subjects initiate ARVs within 30 days after HIV-1 diagnosis, we would need to enroll *72* subjects by the end of the project period to achieve this sample size *(****Figure 5****).* Given our rate of enrollment in recent years, this number would be reasonably expected to accrue within the five years of the project.

Data obtained for this aim will be analyzed by logistic regression using generalized estimating equations (GEE) to account for correlated data and adjusting for the presence of mutations in PBMCs and/or plasma at baseline and the level of detection (<5%, 5-10%, 10-30%, 30-50%, or >50% of the viral quasi-species) of the mutation at baseline. We will also explore differences in the detection of mutations in seminal versus blood plasma and the detection of specific mutations (e.g. M184V) over time in PBMCs, blood and seminal plasma; however, we are unlikely to have sufficient power for these comparisons to perform definitive analyses.

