Guidelines currently recommend HIV-1 drug resistance testing at the time of entry into care [8] even though transmitted mutations detected by consensus sequencing continue to be detected for years following HIV-1 acquisition [9]. HIV-1 surveillance activities of Public Health - Seattle & King County incorporate resistance testing into the care continuum at an even earlier time point, using remnant sera from the initial positive HIV-1 antibody test for consensus sequencing. Results are then communicated to providers of clinical care. If data indicate that low-frequency HIV-1 drug resistance mutations are clinically relevant and are rapidly lost to detection and if more-sensitive assays are developed for clinical use, our public health activities might be tailored to look for low-frequency mutations instead of mutations detected by consensus sequencing.

4. "Also, the PI is urged to be creative in obtaining more subjects since power is a question."

Details in **5. Research Design and Methods** explain that all of the primary objectives are adequately powered with the anticipated sample size. Depending on results of these studies, future grant applications could, for example, generate collaborations with other cohorts of partner-pairs in order to study the transmission of specific mutations (e.g. K103N) in greater depth.

5. "Specifically, the public health importance of the data that would be obtained is still not clear."

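### Aim 1 power: the follow-up table cited as 8c does not follow from the stated 67%/13% retention, and its 89% power applies to 80 resistant subjects when 40 are planned

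*Protocol*

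**What the plan says.** All of this is in Protocol section 5.c.1 unless noted.

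- **Test.** "Power calculations were performed using a two-sided McNemar's exact test with significance level of 0.05".
- **Baseline among resistant subjects**, rounded from the pilot (Table 8a): "25% in PBMCs, 40% in plasma, and 35% having mutations in both PBMCs and plasma".
- **First scenario (Table 8b).** Retention is 100% in PBMCs and 25% in plasma. The follow-up cells are neither 30%, plasma only 10%, PBMCs only 45%, and 15% who "continue to have mutations detected in both PBMCs and plasma". Stated power is 84% with 40 resistant subjects.
- **Second, less extreme scenario (cited as Table 8c, printed under a repeated 8b label).** The text gives retention as "and 67% and 13% of mutations initially detected in PBMCs and plasma remain detectable in follow-up". The printed cells are neither 20 (25%), plasma only 16 (20%), PBMCs only 40 (50%), both 4 (5%). The text concludes "then we would have 89% power to determine whether a significant difference exists", "with 80 subjects who had transmitted HIV-1 drug resistance detected at baseline".
- **Planned size.** The recruitment paragraph adds 16 prospective to 24 previously enrolled resistant subjects, which "would achieve the desired total sample size of 40".
- **Adequacy claim.** Section 1 (Critique #1, item 4) answers a question about power by saying that the design details "explain that all of the primary objectives are adequately powered with the anticipated sample size".

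**The concern.** The second scenario is the only check offered on how the PBMC-versus-plasma comparison fares if the difference is smaller than in Table 8b. A reader needs two things from it: the assumption being tested, and the power at the sample actually planned. The retention percentages in the text and the cells in the table describe different scenarios, so the assumption is unclear. The power is quoted only at twice the planned number of resistant subjects, so the second figure is absent. Depending on which statement is the slip, power at the planned size is either well short of 80% or slightly above it. The general adequacy claim in section 1 depends in part on which one is meant.

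**Working it through.** **Inputs (section 5.c.1).** Baseline: PBMCs only 0.25, plasma only 0.40, both 0.35. So PBMC-positive = 0.25 + 0.35 = 0.60 and plasma-positive = 0.40 + 0.35 = 0.75.

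**Method.** Let p10 be the proportion positive in PBMCs only at follow-up and p01 the proportion positive in plasma only. The number of discordant subjects D is Binomial(n, p10 + p01). Given D, the PBMC-only count is Binomial(D, p10/(p10 + p01)), and the test is the two-sided exact binomial test of 0.5 at 0.05. Power is the rejection probability averaged over D.

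**Step 1: reproduce the stated powers from the printed cells.**

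| Cells | p10 | p01 | n | Computed | Stated |
|---|---|---|---|---|---|
| Table 8b | 0.45 | 0.10 | 40 | 84.4% | 84% |
| Table cited as 8c | 0.50 | 0.20 | 80 | 88.9% | 89% |

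Both stated powers come from the printed cells. The 8c counts (20 + 16 + 40 + 4 = 80) agree with their percentages, so the table is not garbled.

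**Step 2: compare the 8c margins with the stated retention.**

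- From 67%/13%: PBMC-positive = 0.67 × 60% = 40.2%; plasma-positive = 0.13 × 75% = 9.75%.
- From the printed table: PBMC-positive = 50% + 5% = 55%; plasma-positive = 20% + 5% = 25%.
- Retention implied by the table: 55/60 = 92% and 25/75 = 33%.

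Margins do not depend on how losses in the two compartments overlap, so no correlation assumption reconciles these. Rounding is not the cause either: the unrounded pilot counts in Table 8a give 0.67 × 20/34 = 39% and 0.13 × 26/34 = 10%. Reading the figures as losses (13% of PBMC and 67% of plasma detections lost) gives 0.87 × 60% = 52% and 0.33 × 75% = 25%, which still misses the 55%.

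**Step 3: power under each reading.** For 67%/13% with independent losses:

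- both = 0.35 × 0.67 × 0.13 = 0.030
- p10 = 0.402 − 0.030 = 0.372
- p01 = 0.0975 − 0.030 = 0.067

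The overlap can range from both = 0 (p10 = 0.402, p01 = 0.0975) to both = 0.35 × 0.13 = 0.0455 (p10 = 0.3565, p01 = 0.052).

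| Reading | n = 40 | n = 80 |
|---|---|---|
| Printed 8c cells | 55.8% | 88.9% |
| 67%/13%, independent losses | 83.1% | 99.1% |
| 67%/13%, all possible overlaps | 75.9% to 86.7% | 97.7% to 99.5% |

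With the printed cells, power first reaches 80% at n = 64 (80.4%; 79.7% at 63).

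**Step 4: Table 8b.** With 100%/25% retention:

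- PBMCs only = 0.25 + 0.35 × 0.75 = 51.25%
- both = 0.35 × 0.25 = 8.75%
- plasma only = 0.40 × 0.25 = 10%
- neither = 0.40 × 0.75 = 30%

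The printed 45% and 15% are 0.75 × 60% and 0.25 × 60%. That applies the plasma retention to every PBMC-positive subject, including the 25% with no plasma mutation at baseline. With the corrected cells (p10 = 0.5125, p01 = 0.10), power at n = 40 is 92.6%. No overlap assumption is needed here, because PBMC retention is 100%.

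**The case against.** **The 80-subject case is openly a separate scenario.** This stands. The protocol derives 40 from Table 8b, labels the second case as conditional, prints its own n, and nowhere claims 89% at 40. Showing that a smaller effect needs more subjects is ordinary sensitivity reporting. What is missing is the power of that scenario at the planned size.

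**The 89% is right.** It is, for the printed cells at 80. The fault lies in tying it to 67%/13%.

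**The retention may be per mutation.** The first scenario speaks of subjects and the second of mutations, while Table 8 counts subjects with at least one mutation. A subject with several mutations stays positive if any one persists, so subject-level retention could exceed 67%/13%. With independent losses, reaching 92% and 33% would need about 2.2 mutations per subject in PBMCs (1 − 0.33^2.2 ≈ 0.92) and 2.9 in plasma (1 − 0.87^2.9 ≈ 0.33). The pilot averages from Tables 4d and 5 are 33/20 = 1.65 and 32/26 = 1.23. This does not rescue the table, but it means the 83% assumes subject-level retention.

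**The planned analysis is more powerful.** Section 5.c.1 calls the McNemar calculation conservative relative to the planned GEE model. It gives no figure, so the remark cannot be credited with closing a gap from 56% to 80%, and it does not resolve the mismatch.

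**A stronger reading is tempting:** that the design cannot deliver the less extreme scenario, or that Aim 1 needs a larger sample. The documents do not support it. It holds only if the table rather than the text is meant, and nothing says which. Under the text's own retention, 40 subjects give about 83%, and the scenario that sets 40 gains power when corrected.

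**Conclusion.** The point holds as an inconsistency between stated inputs and reported power. The table cited as 8c does not follow from 67%/13% retention on the stated baseline (55% and 25% against about 40% and 10%), and its 89% belongs to twice the planned number of resistant subjects. The size of the consequence is unresolved: 56% power at 40 if the printed cells are intended, or about 83% if the retention text is. The second figure assumes subject-level retention and independent losses within subjects positive in both compartments; over all overlaps it runs from 76% to 87%. The Table 8b slip understates power (84% printed, about 93% from its own retention), so the basis for 40 survives. The passages are wrong as written and should be corrected, but the finding does not show that Aim 1 is underpowered.

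**What to change.** 1. Decide which 8c statement is intended. Either recompute the cells from 67%/13%, or keep the cells and state the retention they imply (about 92% and 33%). Say whether retention is per subject or per mutation.
2. Treat Table 8b the same way: use 51.25% PBMCs only and 8.75% both, with power of about 93%, or state the assumption that produces 45% and 15%.
3. Relabel the second 8b as 8c.
4. Report the power of both scenarios at the planned 40, with the overlap assumption stated. Keep a figure at 80 only if it is marked as beyond the planned sample.
5. If the printed 8c cells are intended, qualify the section 1 statement on adequate power: 40 subjects give 56% in that scenario, and 64 would be needed for 80%.
6. The remark on the conservatism of McNemar's test may stay, but should be quantified or not relied on.

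The cost is text and table edits and a short recalculation. No change to the sample size or design is required.
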